## Abstract

**Background:**

Conventional amblyopia treatment involves the occlusion of the fellow eye using an eye patch. However, this approach imposes a substantial psychological and physical burden on pediatric patients with amblyopia, resulting in low adherence and suboptimal visual outcomes. As responsiveness to therapy declines beyond early childhood, treatments that can enhance adherence and improve efficacy are needed. We developed a virtual reality dichoptic training app (VR app) that integrates gamification and hand-eye coordination training in pediatric patients with amblyopia.

**Objective:**

This study investigated the effect of a VR app on visual acuity improvement in pediatric patients with amblyopia compared with conventional occlusion therapy using an eye patch.

**Methods:**

This is a multicenter, open-label, prospective, randomized controlled trial that will be conducted at 3 centers in Tokyo, Japan. Pediatric patients aged 3-10 years with anisometropic, strabismic, or refractive amblyopia will be enrolled. Participants will be assigned 1:1 to a VR app group or a control group. The VR app group will use the VR app at home for 1 hour per day for 6 months. The control group will undergo conventional occlusion therapy with an eye patch for 6 months. Each group will comprise 15 participants (30 participants in total). Ophthalmologic examinations will be performed at baseline and at weeks 4, 8, 12, 16, 20, and 24. The primary endpoint will be the change in the best-corrected visual acuity in the amblyopic eye from baseline to week 12. Secondary endpoints will include changes in best-corrected visual acuity, stereopsis, and ocular deviation through week 24. We will also assess treatment adherence, defined as the ratio of the cumulative actual treatment time to the cumulative prescribed time; record adverse events, and evaluate usability in the VR app group. Longitudinal changes in outcome measures will be analyzed using a mixed-effects model.

**Results:**

Participant enrollment will start from January 1, 2026, to September 30, 2026. The data analysis will begin on October 1, 2026, and the results will be reported by March 31, 2027.

**Conclusions:**

This study will clarify the effectiveness of the newly developed VR app in improving treatment outcomes and adherence among pediatric patients with amblyopia. By addressing the limitations of conventional occlusion therapy and providing a potentially more efficacious and acceptable treatment option, the VR app may enhance clinical outcomes and represent a paradigm shift in the treatment of pediatric amblyopia.

## Introduction

Amblyopia is primarily characterized by reduced visual acuity in one or both eyes, with a prevalence of approximately 1% to 5% among children worldwide and an estimated prevalence of 0.1% to 0.2% in Japan [1-5]. Pediatric amblyopia is most commonly attributable to refractive errors, anisometropia, strabismus, and visual deprivation [6]. The treatment of amblyopia involves the use of fully corrective glasses in combination with occlusion therapy using an eye patch to train the amblyopic eye. However, the sensitive period of visual development extends only until approximately the age of 7 years [7], after which the effectiveness of treatment becomes significantly limited. Accordingly, amblyopia necessitates public health strategies aimed at early detection, the establishment of effective therapeutic approaches, and efficient management [8].

In Japan, under the Maternal and Child Health Law, all 3-year-old children undergo ophthalmologic screening, including testing for amblyopia, as part of their routine health examination [9]. The screening process is implemented in successive stages. Initially, parents conduct vision testing at home, and the results are submitted to the health examination site. At the venue, pediatricians, in collaboration with public health nurses and other nonophthalmic professionals, review the submitted data and, when indicated, perform supplementary preliminary assessments. If abnormalities are suspected, the child is subsequently referred to an ophthalmology clinic, where ophthalmologists conduct comprehensive examinations [9]. Nevertheless, reports indicate that home-based vision screening overlooks approximately 24.2% of pediatric patients with amblyopia [9]. According to a report assessing vision screening at 30-35 months of age in the United Kingdom, orthoptist-administered screening achieved sensitivities and specificities approaching 100%. Contrastingly, screening performed by healthy visitors yields a sensitivity of only approximately 50%, with approximately half of the affected cases remaining undetected [10]. Accordingly, evidence suggests that certain cases of amblyopia go unrecognized when comprehensive examinations at medical institutions are not undertaken, thereby precluding the timely initiation of appropriate therapy [10].

In occlusion therapy utilizing an eye patch, whereby the healthy eye is covered to promote the use of the amblyopic eye, the duration of daily occlusion must be extended with advancing patient age, thereby imposing an increasing psychological and physical burden on the child [11,12]. Excessive burden associated with amblyopia treatment may result in reduced adherence, manifested by noncompliance with the occlusion of the healthy eye by the child or premature discontinuation of therapy by parents of their own judgment, thereby attenuating the overall effectiveness of amblyopia management [13-15]. A study assessing adherence to occlusion therapy using an eye patch reported that patients complied with the patch wear for approximately half of the prescribed occlusion time [16]. Adherence to amblyopia therapy has been demonstrated to exhibit a dose-response relationship with therapeutic efficacy [17]. Accordingly, the development of alternative modalities to occlusion therapy that lessen the psychological and physical burden, thereby mitigating the decline in adherence, is warranted.

To overcome the challenges associated with pediatric amblyopia therapy, we developed a clinical investigational device, the virtual reality (VR) app, which utilizes VR as a programmatic medical device for amblyopia training in children (Figure 1A) [18]. The VR-based Software as Medical Device (SaMD) for pediatric amblyopia incorporates functionality to partially render the visual input to the healthy eye transparent and includes a gaming module operated through hand-tracking controllers [18]. The VR app enables amblyopia training through interactive gameplay, wherein part of the image projected onto a healthy eye is rendered transparent to facilitate the engagement of the amblyopic eye during the task [18]. An illustrative example of a VR-based SaMD for pediatric amblyopia training is the Luminopia One (Luminopia, Inc.), which was granted authorization by the U.S. Food and Drug Administration [19]. The therapeutic effect of Luminopia One is achieved by attenuating the contrast of visual stimuli presented to the healthy eye, which in turn promotes the use of the amblyopic eye and enhances the efficacy of amblyopia training [19]. The principal difference between Luminopia One and the VR app is that Luminopia One delivers only contrast-modified visual content, whereas the VR app integrates interactive games requiring active physical engagement via hand-tracking controllers, such as kendama (Figure 1A), tennis (Figure 1B), and table tennis (Figure 1C) [18,19]. In contrast to the amblyopia training implemented in Luminopia One, which is limited to passive viewing of visual content with the amblyopic eye, the VR app incorporates VR-based games that require active hand-eye coordination, potentially conferring greater therapeutic efficacy in amblyopia treatment [20]. Thus, the VR app–based amblyopia training may confer greater therapeutic efficacy than conventional approaches, owing to its distinctive advantages: alleviation of psychological and physical burden by obviating the use of an eye patch, improvement of adherence through gamification, and provision of effective training that incorporates hand-eye coordination [17,18,20,21].

This study aims to conduct a multicenter clinical trial to assess the therapeutic effectiveness of a VR app in pediatric amblyopia. The use of the VR app is expected to enable amblyopia training with higher adherence and enhanced efficacy compared to conventional occlusion therapy, with the potential to mitigate the societal burden attributable to pediatric amblyopia.

**Figure 1. F1:**
[figure not shown]
The virtual reality (VR) app for pediatric patients with amblyopia. (A) VR head–mounted display and a screenshot of the Kendama game projected to each eye. In the fellow eye, the ball is displayed as semitransparent. (B) Screenshot of the tennis game projected to the fellow eye. (C) Screenshot of the table tennis game projected to the fellow eye.

## Methods

### The VR Dichoptic Training App for Pediatric Patients With Amblyopia

A VR app for pediatric patients with amblyopia was developed by InnoJin Inc., ImaCreate Co. Ltd., and Sumitomo Corporation. The VR app has not yet been approved as an SaMD in Japan as of August 31, 2025. After being approved for SaMD, pediatric patients with amblyopia will be able to download and use the VR app for pediatric amblyopia on a VR device after receiving a prescription from their physicians.

The VR app for pediatric patients with amblyopia uses a gamification approach to train the amblyopic eye in pediatric patients. Currently, the VR app for pediatric patients with amblyopia provides kendama, tennis, and table tennis games (Figure 1A-C, respectively). Kendama is a children’s activity that uses the traditional Japanese skill toy called “kendama” [22], which consists of a handle (called “ken,” meaning “sword”) and a ball (called “tama” or “dama”) connected by a string. The basic way to play is to catch the thrown ball with 1 of the 3 cups on the handle, or to “spike” the ball by inserting the tip of the handle into a hole on the ball. Countless combinations and styles exist to catch the ball, and players often combine techniques in unique ways to perform tricks. In the VR app, players will wear the VR head–mounted display and swing the controllers, allowing them to move the kendama handle and catch the ball in a virtual world. The “tennis” and “table tennis” games will both be sports in which players hit a ball back and forth with a racket by swinging the controllers to move a racket and hit the ball in the virtual world. This study will use the MeganeX Superlight 8K (Shiftall Inc.) as the head-mounted display.

The VR app will provide amblyopia training within the games. By ensuring that the ball image projected to the healthy eye is semitransparent or transparent, the program replicates the occlusion of the healthy eye and encourages the use of the amblyopic eye while playing the game. Additionally, the VR app for pediatric patients with amblyopia will incorporate hand-eye coordination training using hand-tracking controllers, which may promote the greater development of visual pathways compared with conventional approaches that require only image viewing without physical movement [20].

### Study Setting

This multicenter, open-label, randomized controlled trial is scheduled to be conducted from January 1, 2026, to March 31, 2027. Patients will be enrolled at 3 medical institutions: Toho University Omori Medical Center (Tokyo, Japan), Teikyo University Hospital (Tokyo, Japan), and the CS Eye Clinic (Tokyo, Japan).

### Ethical Considerations

This study has been approved by the Teikyo University Certified Review Board, Tokyo, Japan (protocol version 1.0; August 14, 2025; approval number: C0130-6). The parents of the participating children, acting as their representatives, will provide written informed consent. Informed assent will also be obtained whenever possible from children judged to have at least an elementary school level of understanding. All individuals involved in this study will make every effort to protect the personal information and privacy of the participating patients, and patient data will be anonymized to ensure that no individual can be identified. Participants who complete all study procedures through the final visit at week 24 will be provided with a voucher valued at 20,000 yen (approximately US $128, as of January 5, 2026). Participants who discontinue participation prior to the final visit, after completing at least 12 weeks but fewer than 24 weeks of study participation, will be provided with a voucher valued at 10,000 yen (approximately US $64, as of January 5, 2026).

### Inclusion and Exclusion Criteria

Outpatients who visit the collaborating study institutions will be recruited and must meet the following inclusion criteria: between 3 and 10 years old at time of enrollment; diagnosis of anisometropic amblyopia, strabismic amblyopia, or refractive amblyopia; best-corrected visual acuity (BCVA) of 0.3 logMAR or worse in the amblyopic eye at screening; and have a BCVA in the fellow eye of 0.2 logMAR or better at screening [19]. The inclusion age range was chosen because amblyopia treatment responsiveness declines with age, and improvement is less likely in older children. In this study, limiting enrollment to younger children was considered ethical because the VR-based intervention’s effectiveness remains uncertain.

In this study, amblyopia is confirmed before enrollment, and since anisometropic and refractive amblyopia may occur even with small interocular acuity differences, we did not require a 2-line difference as eligibility criterion, though commonly referenced as a diagnostic indicator of amblyopia [23]. The exclusion criteria will be as follows: inability to obtain consent from the legal guardian; where applicable, inability to obtain assent from the patient; history of intraocular surgery or refractive surgery; history of photosensitive epilepsy; inability to comply with the study protocol due to psychological, familial, or geographic reasons; or inability to perform hand-eye coordination tasks, as determined by physical or mental conditions or by observation during a trial use of the study device, indicating a clear inability to establish hand-eye coordination.

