### Primary Outcome

The primary outcome measure will be that the improvement in BCVA in the amblyopic eye from enrollment to 12 weeks in the VR app group is noninferior to the improvement in BCVA in the amblyopic eye from enrollment to 12 weeks in the control group. This outcome measure will be designed to confirm that the amblyopia treatment effect of the VR-based program is not inferior to that of conventional eye patch therapy. In addition, since previous studies investigating amblyopia treatment using a VR headset have shown a significant treatment effect following 12 weeks of use, comparing BCVA at 12 weeks will enable an efficacy assessment of the VR-based program for amblyopia under standard amblyopia treatment conditions, and thus, the 12-week time point will be adopted [19,34].

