### Sample Size and Statistical Analyses

The primary outcome of this study will be to determine whether the improvement in BCVA from enrollment to 12 weeks in the VR app group is noninferior to the improvement in BCVA from enrollment to 12 weeks in the control group. Based on the assumption that the difference in mean BCVA at 12 weeks between the control and VR app groups will be 0.07 LogMAR [35], the common standard deviation will be 0.14 [36] LogMAR, the noninferiority margin will be 0.10 LogMAR [37], the significance level will be 2.5%, and statistical power will be 90%, a sample size of 24 participants (12 per group) is required [19]. Anticipating a dropout rate of approximately 20%, the target sample size has been set to 30 participants (15 per group).

To assess whether the VR-based program for amblyopia is noninferior to eye patch therapy, the 95% CI for the change in BCVA between 0 and 12 weeks will be calculated for both the control and VR app groups. If the lower bound of the 95% CI for the change in BCVA in the VR app group is greater than that in the control group, the VR-based program for amblyopia will be considered noninferior to eye patch therapy, and the primary outcome criterion will be met.

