This study has certain limitations. First, despite the explicit inclusion criteria specifying participants with anisometropic, strabismic, or refractive amblyopia and a BCVA of ≤0.5 logMAR in the amblyopic eye, heterogeneity in disease severity, underlying etiology, and associated comorbidities may influence therapeutic outcomes. Second, interindividual differences in age, prior exposure to VR devices, and degree of familiarity may have affected both adherence and therapeutic response, especially during the initial phase of the study. To minimize the influence of such heterogeneity, participants allocated to the VR app group underwent an interim visit at week 2—prior to the first ophthalmologic assessment at week 4—during which VR app usage was reviewed to facilitate the proper continuation of treatment, even among participants with limited prior experience using VR systems. Third, the extended use of the VR app carries the potential risk of adverse effects, including VIMS and asthenopia. Our prior safety evaluation of the VR app in adults revealed no VIMS- or vision-related adverse events [18]. However, data on the long-term use of VR apps in pediatric populations remain limited, and the occurrence of adverse events could potentially affect treatment adherence and diminish the therapeutic efficacy of amblyopia management. Fourth, while amblyopia therapy in clinical settings is generally expected to extend beyond the 6-month duration of this study, this protocol does not permit the evaluation of long-term efficacy, posttreatment sustainability of therapeutic benefits, or the risk of amblyopia recurrence. Upon the completion of this study, an extension study is being conducted to allow interested participants to continue treatment with the VR app. The implementation of such a study with an extended follow-up would facilitate the assessment of long-term therapeutic efficacy and safety, persistence of treatment effects, and the likelihood of amblyopia recurrence. Fifth, the VR app–based stereopsis test used here was newly developed without formal validation. From a visual psychophysics perspective, this task uses a 4-alternative forced-choice design with size-constancy adjustments to reduce monocular cues. However, the extent of monocular cue elimination remains unverified. The floor and ceiling disparity levels of this stereotest are undetermined. Therefore, the stereopsis outcomes should be interpreted as preliminary. We included an in-headset stereopsis measure as it may provide a practical way to assess stereopsis under intervention conditions and enable monitoring between clinic visits, with potential utility for future clinical implementation and remote assessment in telemedicine.

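### Children are enrolled past the age at which the protocol says treatment becomes limited, and the primary non-inferiority rule neither uses age nor requires that the control arm improved

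*Protocol article*

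**What the plan says.** All references are to the protocol article.

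- **Introduction:** "the sensitive period of visual development extends only until approximately the age of 7 years", "after which the effectiveness of treatment becomes significantly limited".
- **Inclusion and Exclusion Criteria:** participants are "between 3 and 10 years old at time of enrollment". The reason given is "The inclusion age range was chosen because amblyopia treatment responsiveness declines with age, and improvement is less likely in older children", and the range is presented as a restriction to younger children.
- **Primary Outcome:** the aim is that the 12-week gain in best-corrected visual acuity (BCVA) with VR "is noninferior to the improvement in BCVA in the amblyopic eye from enrollment to 12 weeks in the control group".
- **Sample Size and Statistical Analyses:** a 95% CI for the 12-week change is calculated in each arm. Non-inferiority is declared if the VR arm's lower bound exceeds the control arm's. Age does not enter this rule, and no condition is placed on the control arm's own change. The between-group methods (t tests or mixed models) name no age term. Adjustment for confounding is mentioned only for the gameplay associations.
- **Discussion (limitations):** "interindividual differences in age, prior exposure to VR devices, and degree of familiarity may have affected both adherence and therapeutic response". The mitigation offered is the week-2 visit in the VR arm, which reviews use of the device.

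**The concern.** In a superiority trial, patients who respond poorly to both treatments make success harder. In a non-inferiority trial they can make it easier, because they contribute a difference near zero whichever treatment is better for everyone else. By the article's own account, children aged 8 to 10 are past the age at which response becomes limited, and age is a driver of response.

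Two protections would normally stand against this: evidence that the active control worked in the population enrolled, and some view of the comparison by age. The primary rule contains neither. A positive result could then mean that both treatments worked about equally, or that neither did much, and the rule would not tell these apart.

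**Working it through.** **Inputs.** Margin 0.10 logMAR, assumed difference 0.07, SD 0.14, significance level 2.5% (taken as one-sided), power 90%, 12 evaluable per group and 15 enrolled, all from Sample Size and Statistical Analyses. The share f of children showing no arm difference is not given. I assume 25% to 50%. Even enrolment over the eight year-groups 3 to 10 would put 3/8 = 37.5% at ages 8 to 10.

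**The plan's own figure.** The assumptions are "the difference in mean BCVA at 12 weeks between the control and VR app groups will be 0.07 LogMAR" and "the common standard deviation will be 0.14". If VR is better by 0.07, n per group = 2 × (1.960 + 1.282)² × 0.14² / (0.10 + 0.07)² = 14.3, so 15, not 12. The direction of the 0.07 is not stated, and with VR worse by 0.07 the number is 458. The dropout step does reproduce: 24 / 0.8 = 30. This mismatch is a separate matter. I use 12 per group below because it is the plan's figure.

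**Dilution in a standard margin test.** If VR is worse by D in responsive children and equal in a fraction f, the overall deficit is D × (1 − f). The standard error is 0.14 × √(2/12) = 0.0572. The chance of concluding non-inferiority is the noncentral-t probability with 22 degrees of freedom and noncentrality (0.10 − D(1 − f)) / 0.0572.

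| f | Overall deficit, D = 0.10 | Chance of passing | Overall deficit, D = 0.15 | Chance of passing |
|---|---|---|---|---|
| 0 | 0.100 | 2.5% | 0.150 | 0.3% |
| 25% | 0.075 | 6.2% | 0.1125 | 1.5% |
| 37.5% | 0.0625 | 9.1% | 0.094 | 3.2% |
| 50% | 0.050 | 13.1% | 0.075 | 6.2% |

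**The other direction.** If VR is better by 0.07 in responsive children, the same formula gives power of 81% at f = 0, 72% at 25%, 67% at 37.5% and 62% at 50%.

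**The rule as written.** I score improvement as positive and simulate the comparison of lower bounds with 12 per arm and SD 0.14. For D = 0.10 the chance of declaring non-inferiority is about 5.6%, 11.6%, 16.0% and 21.2% at the four values of f. When neither arm changes and spread is equal, it is about 50%. That follows from symmetry: with identical arms, either lower bound is equally likely to be the higher. The same 50% arises when both arms improve equally, so the rule cannot separate these two situations.

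**Effect of a control-arm condition.** If the control arm truly does not change, its 95% CI lies wholly above zero 2.5% of the time, so a false claim in that situation falls from about 50% to at most 2.5%. The control half-width is 2.201 × 0.14 / √12 = 0.089, so an observed control gain above about 0.089 logMAR is needed. This applies the plan's SD to the within-arm change.

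**The case against.** The strongest reply has five parts.

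1. **The text does not say that older children are untreatable.** It says effectiveness is limited and improvement less likely, and a cap at 10 can fit a gradual decline. This stands. A reader might infer that neither treatment works after 7, and the article does not support that. Both f and the zero arm difference in those children are assumptions.
2. **A diluted deficit inside the margin does not pass by itself.** This stands. A reader might take an overall deficit of 0.094 as success. The 95% half-width for the difference is 2.074 × 0.0572 = 0.119, so the observed result would have to favour VR by about 0.02, and the chance of that is 3.2%.
3. **The control arm's change is examined.** Within-group BCVA comparisons are planned under Secondary Outcomes, and the control CI is calculated for the primary analysis. This stands, so it would be wrong to say that nothing checks the control. What is absent is any bearing of that check on the non-inferiority claim.
4. **Stratification, covariates and subgroups may sit in the full protocol or SAP.** This stands. Their absence from a journal article is not an error, and it does not show that allocation ignores age. The primary success rule, however, is stated in full.
5. **The study calls itself exploratory and foresees confirmatory trials.** True, but the exploratory label is attached to the secondary outcomes, and the primary criterion is still declared met or not met.

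**Conclusion.** The point holds as a moderate weakness of the stated primary rule. The article's account of age and response sits uneasily with an upper limit of 10, and the limitation it admits about age is answered only by a visit that addresses device use.

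In a standard test, a true 0.10 logMAR deficit in responsive children would pass about 6% to 13% of the time instead of 2.5%, if 25% to 50% of participants show no arm difference. The true share and the older children's response are unknown. With larger true deficits the chance of a false pass is smaller, and if VR is better the same mechanism works against it. These figures do not show that the trial is likely to succeed for the wrong reason.

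The firmer part does not depend on the age mix: the rule as written gives about a 50% chance of declaring non-inferiority when neither arm responds and spread is equal.

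**What to change.** 1. **Condition on the control arm.** Add to Sample Size and Statistical Analyses that non-inferiority is claimed only if the control arm's 12-week 95% CI, already planned, shows improvement, and that otherwise the result is reported as uninformative. The cost is that a modest but real control gain could miss the bar of about 0.089 logMAR at 12 per arm. The condition shows that the control arm improved, not that patching alone caused it, since both arms wear full-correction glasses.
2. **Age as a covariate.** Include age at enrolment, already collected (Textbox 1), in the week-12 between-arm comparison of BCVA. This helps precision and guards against chance imbalance. It does not undo dilution.
3. **Descriptive result by age.** Show the between-arm difference for children up to 7 beside the overall result. Under even enrolment this is about 5/8 × 15 ≈ 9 per arm, too few to judge a 0.10 margin, so it should carry no test.
4. **Reconcile the age statements** in the Introduction and in Inclusion and Exclusion Criteria. I take no view on which age limit is right.

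The number enrolled and the data collected are unchanged. The claim may become narrower.
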